**Table 4 Tab4:**

Binary items used in the SURE screening tool to assess decisional conflict

If a patient answers “no” to 1 or more questions, then the screen is considered positive for decisional conflict. Understanding decisional conflict is important to ensure that the information provided by *SMART Choice* is presented with clarity and aids the overall experience for patients on their TKA journey.

All participants will have free access to the *SMART Choice* tool at the completion of the study period.

### Sample size and recruitment

Previous studies have estimated baseline willingness for surgery in TKA candidates to be approximately 70% [31]. With the use of first-line interventions, such as therapy groups, willingness to undergo surgery was reported to decrease by 35% at 12 months [32]. We expect our cohort to have a lower baseline willingness for surgery, considering that we will have a significant proportion of participants recruited at the earlier (and less severe) stage of knee OA. We also expect our tool to have a greater impact on willingness to undergo surgery, especially for participants who were earlier in the TKA journey. To detect an absolute change in willingness to undergo surgery from 65 to 50%, a sample size of 169 participants in each arm was required based on calculations using a two-sided t-test at the 5% level of significance with 80% power. To account for a higher-than-expected loss to follow-up proportion due to the online nature of the tool, a 20% inflation of the sample size was added. This resulted in a target enrolment of 200 participants in each arm for a total sample size of 400 participants.

The sample size calculated is a feasible number to recruit because SVHM performs approximately 400 TKAs each year, and HCF has approximately 50,000 members with knee OA. We will aim to recruit 200 patients from the SVHM cohort and approach a random pool of 200 patients with knee OA from the HCF client database. Based on these calculations, we estimate that 6 months will be sufficient time for recruitment to be completed, with a total study time estimate to be 21 months (Fig. 3).

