### Randomisation, allocation, and blinding

Participants will be randomly allocated in a 1:1 ratio into two groups: intervention and treatment as usual (TAU). Allocation will be performed using a computer-generated simple randomisation schedule of consecutive patients. The randomisation will be embedded into the web-based platform that hosts the study portal. All participants who meet the eligibility criteria will be randomised.

Due to the nature of the study, participants will remain unblinded from their allocation group. However, limited disclosure of allocation groups will be applied to prevent participants who are allocated to TAU from proactively seeking out online prognostic tools to use. Investigators (excluding research assistants who will not be involved in data analysis) will remain blinded to the allocation group and identity of patients until after final data analysis is performed. Surgeons will be blinded to the allocation group of their patients and will have no influence on the outcome of allocation or intervention.

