### Statistical plan

Willingness to undergo surgery will be evaluated by intention-to-treat analysis. Although there is no risk that participants in the TAU group will use the *SMART Choice* tool, there is a possibility that participants in the TAU group may seek alternative prognostic tools online. Limited disclosure in the consenting process will help to reduce participants who use alternative tools. Secondary analysis will assess the optimal timepoint for *SMART Choice* tool use. Data on the timepoint each participant is along the TKA journey will help facilitate this. Lost-to-follow-up participants will be included in the final analysis using multiple imputation methods. Categorical outcomes will be compared between groups using chi-squared tests. Relative differences in proportions between the intervention and TAU groups will be calculated as a relative risk with 95% confidence intervals. If there was an imbalance in variables associated with willingness and unwillingness to undergo surgery, logistic regression will be used to assess dichotomous outcomes and reported as odds ratios with 95% confidence intervals. Analysis of continuous outcomes will be performed with 2-sample and 2-tailed Student’s t-tests. Similarly, if there is an imbalance in variables associated with willingness and unwillingness to undergo surgery, continuous outcomes will be assessed using linear regression. We will employ a research assistant to support a high follow-up proportion of patients with respect to completing regular assessments, with a feasibility target of greater than 85%. All statistical analyses and model building will use RStudio software with the “tidyverse” packages.

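### The target of 200 per arm is not 169 inflated by 20% (that gives 203); it is an 18.3% inflation that covers at most about 15.5% loss to follow-up

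*Protocol article*

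**What the plan says.** Protocol article, Sample size and recruitment. The planning effect is given as "To detect an absolute change in willingness to undergo surgery from 65 to 50" per cent, using a "two-sided t-test at the 5% level of significance with 80% power". On that basis "a sample size of 169 participants in each arm was required". The reason for enlarging this number is put as follows: "To account for a higher-than-expected loss to follow-up proportion due to the online nature of the tool". No expected loss rate is given. The step itself reads "a 20% inflation of the sample size was added. This resulted in a target enrolment of 200 participants in each arm", for a total of 400.

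Protocol article, Statistical plan. A research assistant is to support follow-up, "with a feasibility target of greater than 85" per cent. The same section says that participants lost to follow-up will enter the final analysis through multiple imputation.

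**The concern.** The article presents 200 per arm as the outcome of a defined operation on 169, with no mention of rounding or approximation. The operation gives a different number, so the derivation cannot be followed as printed.

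The 20% is also introduced as cover for loss to follow-up. A reader may therefore take it that the trial keeps its power with 20% of participants lost. The enrolment target does not provide that, and the article does not say how much loss it does cover. What is at stake is a correct account of the margin: at what level of loss planned power begins to fall below 80%.

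**Working it through.** **Inputs.** Willingness of 65% against 50%, two-sided 5% level, 80% power, 169 per arm, 20% inflation and 200 per arm, all from Sample size and recruitment. Allocation is 1:1 (Randomisation, allocation, and blinding). The follow-up target is above 85% (Statistical plan).

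**Step 1: reproduce 169.** The usual two-proportion formula with pooled variance under the null is

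n = [1.960 × √(2 × 0.575 × 0.425) + 0.842 × √(0.65 × 0.35 + 0.50 × 0.50)]² / 0.15² = 169.3.

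The arcsine version gives 169.1, the unpooled version 166.6, and a t-test on the arcsine effect size 170.1. The base figure of 169 therefore reproduces, and the fault lies only in the next step.

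**Step 2: apply the stated inflation.**

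- 169 × 1.20 = 202.8, so 203 per arm (406 in total).
- The inflation actually used is 200 / 169 = 1.183, or 18.3%.
- The difference is 3 per arm, or 1.5% of 203.

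**Step 3: find the loss that 200 per arm can absorb.**

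- 1 − 169/200 = 15.5%.
- A full 20% inflation would absorb 1 − 1/1.20 = 16.7%. An inflation of n by 20% is thus not the same as protection against 20% loss.

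**Step 4: power with 200 enrolled per arm** (pooled formula, completers only).

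| Loss to follow-up | Completers per arm | Power, 65% vs 50% |
|---|---|---|
| 15% (edge of the follow-up target) | 200 × 0.85 = 170 | 80.2% |
| 16.7% (what a full 20% inflation would cover) | 200 / 1.20 ≈ 167 | 79.4% |
| 20% (not stated in the article) | 200 × 0.80 = 160 | 77.7% |

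At 160 per arm the arcsine formula gives 77.8% and the unpooled formula 78.4%. "About 78%" is therefore a fair summary.

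**The case against.** The strongest case on the other side is that this is rounding. The literal shortfall is 3 per arm. At the 16.7% loss that a full 20% inflation would cover, power is 79.4% instead of 80%, or about half a percentage point. The rates of 65% and 50% are far less certain than that. This stands, and it is why the point is minor. It does not make the sentence correct, because the article says that the inflation resulted in 200 and does not say that it was rounded.

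Three stronger readings are tempting, and the article supports none of them.

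- **That 212 per arm is needed.** This comes from 169 / 0.80 = 211.25 and treats 20% as the expected loss. The article states an inflation of the sample size and gives no loss rate.
- **That the stated 80% power is not met.** This also needs 20% loss. At the only retention figure in the article, 85%, there are 170 completers, above the required 169.
- **That the 20% and the 85% contradict each other.** One multiplies the sample size and the other is a retention goal. A 20% inflation covers up to 16.7% loss and the target implies loss below 15%, so the two are compatible.

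It can also be said that a completers-only power figure is not the planned analysis, since lost participants will be imputed. Willingness is also asked at baseline, 6 weeks and 12 weeks, so imputation may recover some information. How much cannot be worked out from the article, and the article itself enlarges the sample for loss. The completers-only figures are a reasonable and slightly cautious guide.

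**Conclusion.** The point holds as a minor arithmetic error in the sample-size derivation. A 20% inflation of 169 is 203, not 200. The figure of 200 is an 18.3% inflation and keeps 169 evaluable per arm only up to about 15.5% loss. At the article's own follow-up target, planned power of 80% is kept, with a margin of one completer per arm (170 against 169).

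The figure of about 78% power is conditional on 20% loss, which is an illustration and not a planning assumption of the trial. All power figures assume rates of 65% and 50%, a two-sided 5% test, equal loss in the two arms, and no information from those lost. Nothing here calls for more participants or for a change in analysis.

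**What to change.** Keep 400 participants and correct the sentence under Sample size and recruitment, for example:

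> Enrolling 200 per arm (about 18% above 169) allows for up to about 15% loss to follow-up, consistent with the follow-up target of more than 85%, with 80% power; at 20% loss, power would be about 78%.

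This ties the allowance to the target in the Statistical plan and tells the reader where the margin ends. The cost is wording only, and the stated allowance becomes slightly less favourable than the 20% now printed. No design, conduct or analysis step changes.

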**Fig. 3 Fig3:**
[figure not shown]
Gantt Chart detailing the timeline of the study. ANZCTR: Australian and New Zealand Clinical Trials Registration

### Data collection and management

The *SMART Choice* tool will be housed on a secure web-based platform accessible by participant account credentials only. Data captured from the *SMART Choice* tool will be linked with a participant account and deidentified. Regular assessments will be completed electronically via a secure online study portal using the same participant account credentials. All data will be entered electronically onto the database software REDCap (Research Electronic Data Capture). Hardcopy data for participants who require mail delivery will be entered manually onto REDCap by a research assistant. Access to the REDCap database will be restricted to researchers with staff credentials who are directly involved with the project. The data servers will be housed in secure facilities at SVHM and The University of Melbourne for participants recruited from SVHM and HCF, respectively. All data servers will be physically located in Australia to comply with local privacy laws and regulations. Hardcopy data will be kept in a secure facility with electronic swipe card access at SVHM Clinical Sciences Building. Wireless network access is encrypted using secure enterprise WPA2 encryption. All data will be retained for a period of 7 years from completion of the study and then destroyed permanently.

### Statistical plan

Willingness to undergo surgery will be evaluated by intention-to-treat analysis. Although there is no risk that participants in the TAU group will use the *SMART Choice* tool, there is a possibility that participants in the TAU group may seek alternative prognostic tools online. Limited disclosure in the consenting process will help to reduce participants who use alternative tools. Secondary analysis will assess the optimal timepoint for *SMART Choice* tool use. Data on the timepoint each participant is along the TKA journey will help facilitate this. Lost-to-follow-up participants will be included in the final analysis using multiple imputation methods. Categorical outcomes will be compared between groups using chi-squared tests. Relative differences in proportions between the intervention and TAU groups will be calculated as a relative risk with 95% confidence intervals. If there was an imbalance in variables associated with willingness and unwillingness to undergo surgery, logistic regression will be used to assess dichotomous outcomes and reported as odds ratios with 95% confidence intervals. Analysis of continuous outcomes will be performed with 2-sample and 2-tailed Student’s t-tests. Similarly, if there is an imbalance in variables associated with willingness and unwillingness to undergo surgery, continuous outcomes will be assessed using linear regression. We will employ a research assistant to support a high follow-up proportion of patients with respect to completing regular assessments, with a feasibility target of greater than 85%. All statistical analyses and model building will use RStudio software with the “tidyverse” packages.

### Ethics, registration and dissemination

This study has been approved by the Human Research Ethics Committees at both St. Vincent’s Hospitals, Australia (HREC 285/21), and The University of Melbourne (2021–23,157–24,025-2). This includes the questionnaire data for *SMART Choice* user experience. The University of Melbourne ethics approval pertains to participants recruited from the HCF cohort. Modifications to the protocol that impact the study procedure or analysis will be amended on both the protocol and the ethics application. The study has also been prospectively registered with the Australian and New Zealand Clinical Trials Registry (ACTRN12622000072718). There are no restrictions on the dissemination of results for this study, apart from acknowledgement of funding from the HCF Research Foundation. We plan to disseminate the results through peer-reviewed publications and conference presentations.

## Discussion

*SMART Choice* is not the first prognostic tool to be developed for use in TKA [33, 34]. However, to our knowledge, this will only be the second clinical trial evaluating the effect of a prognostic tool on patient decision making in TKA [35]. This is an important milestone in the implementation of such prognostic tools in clinical practice. A significant barrier to widespread prognostic tool use is the lack of data validating the performance and influencing these tools on patients in a pragmatic setting. By the nature of prognostic tool development, validation is often limited to internal subsets used to test the predictive model. The results from this trial will inform the arthroplasty community with evidence to support or refute the use of the *SMART Choice* tool in clinical practice.

We developed the *SMART Choice* tool with a patient focus in mind. Alternative prognostic tools have historically skewed towards the surgeon or clinician as the preferred user [34, 36–44]. This included predictors that were difficult for patients to input, such as knee range of motion, Kellgren-Lawrence score for X-ray findings, and blood markers. The *SMART Choice* tool aims to simplify the predictive variables to those a patient can input without clinician assistance. The rationale behind this design decision was based on our hypothesis that earlier use of prognostic tools in the TKA journey resulted in more influence on patient decision making. However, a major limitation of our prognostic tool design is the elimination of surgical and clinical factors that may have a bearing on the overall predictive outcome for TKA.

There are other important limitations to this study. Alternative prognostic tools for TKA, such as *After My Surgery,* are freely available for use on the internet [28]. Through participation in the study, participants may be incentivised to use alternative prognostic tools to compare their TKA outcome predictions. Although limited disclosure consent will be used to minimise the risk for this, we expect some participants to still access alternative prognostic tools. The consequence of this practice may present as difficulty isolating the results of this trial to the *SMART Choice* tool. An additional limitation stems from the expectation that participants who are considering TKA are generally in the older age category. The heavy reliance on technology in this study using study portals and online *SMART Choice* tool platforms may be seen as a barrier to participation. Nonetheless, we maintain an online approach for this study, as it reflects the pragmatic environment within which future usage of these tools are likely to exist. In addition, the decision quality questionnaires of the study will help us understand the user experience and how the tool works to change patient expectations around surgery. Furthermore, as a nested qualitative study, we will conduct semi-structured interviews to evaluate the patient experience when using the *SMART Choice* tool. Consequently, this will aid improvements in future versions of the tool.

In summary, we believe our study sets the framework for transitioning the *SMART Choice* tool as an academic body of work into a clinically usable prognostic tool. With the shifting paradigm in surgery towards “individualised care”, the *SMART Choice* tool aims to provide patients with an individualised prediction for TKA outcome. With the use of this tool, the delicate balance of surgical decision-making swings towards patients who can make more informed decisions about their own healthcare needs. Concurrently, clinicians can use this tool to help patients readjust their expectations prior to surgery. Future work in the field of predictive technologies will likely require a high level of scrutiny through clinical trials. Our study is an early step towards progressing the *SMART Choice* tool to be implemented in routine clinical practice.

## Data Availability

Not applicable.

## Abbreviations

ANZCTR: Australian and New Zealand Clinical Trials Registry
BMI: Body mass index
EQ-5D-3L: Euroqol 5-dimensional 3-level survey
GP: General practitioner
HCF: Hospital Contributions Fund (private health insurance company)
HRQoL: Health related quality of life
K-DQI: Knee Decision Quality Instrument
MCID: Minimal clinically important difference
OA: Osteoarthritis
PICF: Participant information sheet and consent form
PROM: Patient reported outcome measure
REDCap: Research Electronic Data Capture software
SMART: St. Vincent’s Melbourne Arthroplasty Outcomes (Registry)
SoA: Schedule of Assessments
SPIRIT: Standard Protocol Items for Randomised Trials
SURE: Decisional conflict screening tool
SVHM: St. Vincent’s Hospital, Melbourne
TAU: Treatment as usual
TKA: Total knee arthroplasty
TRIPOD: Transparent Reporting of Multivariable Prediction Model for Individual Prognosis or Diagnosis
VR-12: Veterans-Rand 12 Survey
WPA2: Wi-fi Protected Access v2
